#### Outcome Assessment and Blinding

Except for the TCM evaluation forms (Multimedia Appendix 1, Figures S4 and S5), the remaining outcome measures will be measured by blinded outcome assessors. All outcome assessors will receive training prior to study initiation to ensure good inter- and intraobserver reliability, particularly for the functional performance testing. Patients will be instructed not to reveal their allocation to the outcome assessors. Outcome assessment will be conducted at the TTSH physiotherapy clinic. Unblinding will be carefully considered and justified in each case of medical emergency or clinical treatment decisions that require the intervention to be known, following the study protocol and ethical guidelines.

#### Sample Size Calculation

The sample size needed to find a 10-point difference for KOOS-12 (the primary outcome) between the intervention and control arms with a power of 90%, a *P* value of .05 (2-sided) and an SD of 14 is n=42. The 10-point difference is based on the minimal clinical important difference for KOOS [42]. The anticipated baseline and SD are based on studies done in similar populations. Accounting for a 20% drop-out rate, a total of 100 patients will be needed for the study.

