**Methods:**

A multicenter, pragmatic, parallel-arm, single-blinded, effectiveness-implementation hybrid randomized controlled trial will be conducted. We intend to recruit 100 patients with KOA randomized to either the control arm (standard care only) or intervention arm (acupuncture with heat therapy, in addition to standard care). The inclusion criteria are being a community ambulator and having primary KOA, excluding patients with secondary arthritis or previous knee replacements. The primary outcome measure is the Knee Osteoarthritis Outcome Score at 6 weeks. Secondary outcome measures include psychological, physical, quality of life, satisfaction, and global outcome measures at 6, 12, and 26 weeks. A mixed method approach through an embedded process evaluation will facilitate large-scale implementation. An economic evaluation will be performed to assess financial sustainability.

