#### Randomization and Concealment of Allocation

Patients who consent to participate will be randomized in a 1:1 allocation ratio to intervention or standard care using a stratified, permuted, block randomization method (block sizes of 4, 6, and 8). Stratification is based on gender with a female to male ratio of 2:1. The unbalance ratio was based on the World Health Organization’s estimate of the prevalence of symptomatic osteoarthritis for people aged 60 years or older, among whom the prevalence of women is almost double that of men (male vs female: 9.6% vs 18%) [17]. The allocation sequence is generated by an independent statistician a priori using Stata (version 16.1; StataCorp) and will be kept concealed from the study team. Randomization will be done using the REDCap (Research Electronic Data Capture; Vanderbilt University) randomization module based on the allocation sequence; allocation will be locked once assigned. Randomization and intervention allocation will only be performed by the study team after the patient is counselled fully about the study and provides informed consent.

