#### Outcome Measures

The choice of outcome measures is based on the OARSI guidelines for lifestyle diet and exercise clinical trials in osteoarthritis [38]. The recommended core outcomes include pain, physical function, and global patient assessment. Additional outcomes include health-related QOL and global physician assessment. Outcome measures will be collected at baseline (pretreatment), week 6, week 12, and week 26. The primary end point in this study is the Knee Osteoarthritis Outcome Score (KOOS-12) at week 6. KOOS-12 is a specialized tool designed to evaluate patients’ knee condition, and it assesses the short- and long-term effects of knee injuries [39]. It reduces respondent burden by 70% from the original KOOS while providing scale scores for knee-specific pain, function, and QOL, along with a summary measure of overall knee impact [40]. The KOOS score has been validated in Singapore [39,41].

Baseline measures such as demographics, socioeconomic status, medical comorbidities, knee symptoms, radiographic severity, height, and weight will be collected.

Additionally, after considering the progression and severity of KOA as defined in TCM clinical guidelines published in China (Multimedia Appendix 1, Figure S3), 2 evaluation forms have been designed. The Knee Osteoarthritis TCM Evaluation Form (Multimedia Appendix 1, Figure S4) was specifically created to integrate the KOOS-12 knee survey with questions based on TCM syndrome differentiation for KOA. This will enable the investigators to assess the efficacy of the treatment by analyzing syndrome differentiation. This form will be administered at week 1 (start of treatment, before the first acupuncture session), week 4 (midtreatment, before the seventh acupuncture session) and week 6 (end of treatment, after the 12th or last acupuncture session). The Knee Osteoarthritis Visual Analog Scale and Range of Motion Evaluation Form (Multimedia Appendix 1, Figure S5) will be administered before and after each of the 12 biweekly acupuncture sessions over 6 weeks.

Clinical data (glycated hemoglobin, blood pressure, and other chronic disease parameters) and operational and cost data (health care use) will also be obtained through the health care administrative databases for economic evaluation.

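### The total of 100 does not follow from 42 per arm with 20% drop-out, which gives 105; the resulting loss of power is small, about 1 to 1.6 percentage points

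*Protocol article*

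**What the plan says.** The Sample Size Calculation section of the protocol article begins "The sample size needed to find a 10-point difference for KOOS-12 (the primary outcome) between the intervention and control arms". It sets power at 90%, a two-sided significance level of 0.05 and a common SD, and reports the result as "an SD of 14 is n=42". The number is not labelled as per arm or in total. The paragraph ends: "Accounting for a 20% drop-out rate, a total of 100 patients will be needed for the study". No inflation formula is shown.

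Three other places bear on this:

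- Randomization and Concealment of Allocation: patients are "randomized in a 1:1 allocation ratio to intervention or standard care".
- Outcome Measures: "The primary end point in this study is the Knee Osteoarthritis Outcome Score (KOOS-12) at week 6".
- Abstract, Methods: the same target is repeated, "We intend to recruit 100 patients with KOA randomized to either the control arm".

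**The concern.** A drop-out allowance should leave the required number of evaluable patients after the losses. Taking 20% off 100 leaves 80, or 40 per arm. That is fewer than the 42 which the same paragraph says are needed, so the last step of the calculation contradicts the step before it.

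What is at stake is the accuracy of the justification for the primary comparison. The article commits to CONSORT reporting, so this paragraph is likely to reappear in the results paper, where the mismatch can be seen in one line of arithmetic. The missing per-arm label also leaves the reader to guess how 42 becomes 100.

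**Working it through.** **Inputs** (Sample Size Calculation, except the allocation ratio): difference 10 points; SD 14; power 90%, z = 1.2816; two-sided alpha 0.05, z = 1.960; drop-out 20%; stated total 100. Allocation is 1:1 (Randomization and Concealment of Allocation).

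**Step 1. Reproduce the 42.**

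n per arm = 2 × (1.960 + 1.2816)² × (14/10)² = 41.19, rounded up to 42. The t-test solution is 42.17. The stated figure therefore reproduces as a per-arm number, and the evaluable total is 2 × 42 = 84. It cannot be the total: 21 per arm would give only 63.9% power (normal approximation) or 61.7% (t-test).

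**Step 2. Allow for 20% drop-out.** If a fraction d is lost, the number to randomize is N = n / (1 − d).

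| Starting point | Calculation | N |
|---|---|---|
| Stated 42 per arm | 84 / 0.80 | 105 (106 for equal arms) |
| Unrounded normal formula | 2 × 41.19 / 0.80 = 102.98 | 103 |
| Unrounded t-test | 2 × 42.17 / 0.80 = 105.4 | 106 |
| Multiplying instead of dividing | 84 × 1.2 | 100.8 |

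The first three rows all exceed 100. Rounding the t-test figure up to 43 per arm first would give more still (86/0.80 = 107.5). Only the last row comes near the stated total. Since the article shows no formula, that origin is an inference; the mismatch is not.

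**Step 3. Power at the stated total.** With 20% of 100 missing, 80 remain, 40 per arm.

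Normal approximation: 10 / (14 × √(2/40)) = 3.194; 3.194 − 1.960 = 1.234; power = Φ(1.234) = 89.1%.

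| Evaluable per arm | Normal approximation | t-test |
|---|---|---|
| 40 (100 randomized, 20% lost) | 89.1% | 88.4% |
| 42 (the plan's requirement) | 90.5% | 89.9% |
| 50 (100 randomized, none lost) | 94.6% | 94.3% |

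Against the stated 90%, the shortfall at 40 per arm is 0.9 points (normal approximation) or 1.6 points (t-test). If losses vary at random between and within arms, rather than being exactly 10 in each, average t-test power is 88.2%. By the normal approximation, the difference detectable with 90% power at 40 per arm is 14 × √(2/40) × 3.2416 = 10.15 points; by the t-test it is 10.27. The planned difference is 10.

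**Step 4. Drop-out that 100 can absorb.** 1 − 84/100 = 16%. At that rate 42 per arm remain, with power 90.5% (normal approximation) or 89.9% (t-test), so about 90%.

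**The case against.** The strongest reply is that nothing of consequence follows. A gap of 0.9 to 1.6 points of power is smaller than the uncertainty in the SD of 14, and the detectable difference moves by less than 0.3 points. The total of 100 is stated consistently in the Abstract and in the Sample Size Calculation, and 65 patients were already enrolled by November 6, 2023. No analysis or decision rule depends on the missing five patients. This stands, and it makes the point minor. It does not make the arithmetic right.

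A second reply concerns timing. The primary endpoint is at week 6 while follow-up runs to week 26, and the 20% is not tied to a visit. If it means loss over the whole 26 weeks, more than 80 patients may have week-6 data, and the requirement of 84 could be met. This also stands. The computed power is therefore conditional on 20% being missing at week 6.

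A third reply is that the per-arm reading of 42 is obvious, since only that reading reproduces under 1:1 allocation. That is true, and the missing label would not deserve a comment by itself. It is worth adding only because the sentence needs correcting anyway.

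Two stronger readings are tempting, and the article supports neither:

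- *The trial is underpowered.* A reader might infer this from 80 being fewer than 84. Power is still 88% to 89% under the plan's own inputs.
- *Adjusting for baseline KOOS-12 recovers the loss.* If SD 14 describes the week-6 score, adjustment scales the required number by 1 − r², where r is the correlation between baseline and week 6. To bring it down to 40 per arm, r² must be at least 1 − 40/41.19 = 0.029 (r about 0.17, normal approximation) or 1 − 40/42.17 = 0.051 (r about 0.23, t-test). But the article gives no correlation and does not say whether SD 14 is for the score or for the change. The Data Analysis Plan already works with change from baseline, so any further gain may be smaller.

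**Conclusion.** The stated total contradicts its own inputs. With 42 per arm and 20% drop-out, 105 patients are required (106 for equal arms, 103 if nothing is rounded before the last step), not 100. This is a small arithmetic error in the inflation step, with almost no effect on the trial: power falls from the stated 90% to 89.1% (normal approximation) or 88.4% (t-test).

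The conclusion rests on three assumptions: 42 is per arm, which the recalculation supports; the full 20% is missing at week 6, which the article does not say; and the comparison is a plain two-sample one with SD 14. The 16% limit in Step 4 should not be read as an exact threshold for 90% power, because by the t-test 42 per arm falls just short of 90%.

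**What to change.** Keep the target of 100 and restate the end of the Sample Size Calculation paragraph, for example:

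> 42 per arm (84 evaluable). With 100 randomized, 84 remain evaluable at week 6 if drop-out is up to 16% (power about 90%); at 20% drop-out (40 per arm) power is about 88% to 89%.

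It would help to say which visit the drop-out rate refers to. If the sponsor wishes to add that baseline adjustment offsets the loss, it should be marked as an assumption that depends on the correlation between baseline and week 6 and on whether SD 14 is for the score or the change.

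The cost is one or two sentences and a slightly less favourable power statement. No further patients, and no change to the design or the analysis, are needed.

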#### Data Analysis Plan

Results will be analyzed by the intention-to-treat principle. However, data will also be analyzed by a per-protocol approach to account for protocol violations, such as patients who were deemed not compliant to treatment or patients who underwent a surgical procedure of the knee due to treatment failure during the study. Descriptive frequency analysis will be used for baseline characteristics. For continuous variables, the mean and SD will be reported and for categorical variables, the frequencies and percentages will be reported. Between-group comparisons of change from baseline to the 26-week follow-up in the primary and secondary continuous outcomes will be analyzed using a generalized linear mixed model (GLMM). Testing for normality of distributions of outcomes will be based both on the Shapiro-Wilks test and a visual analysis of the histogram plot. Categorical secondary outcomes will be analyzed using the ordinal logistic regression function under the GLMM. A 2-sided *P* value less than .05 will be considered statistically significant. An analysis will be done on the nature of the missing data to determine if the data are missing at random or a systemic bias is present resulting from the missing data.

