#### Treatment Regimen

The patient will be treated in a supine position with pillows under both knees. After a standard disinfection procedure, a 30 × 40–mm disposable stainless steel acupuncture needle (YangTzeKing Impex S Pte Ltd) will be inserted according to the location defined; the direction of insertion and the safe depth range are specified in Multimedia Appendix 1, Figure S2 [21, 30,31]. Basic manipulations such as lifting and thrusting, twirling, and rotating are applied until the needling sensation (*de-qi*) is obtained. After *de-qi* is obtained, uniform reinforcing-reducing (平补平泻) manipulations are applied. The needles will be retained for 30 minutes (except for weizhong [BL40], where the needle is removed immediately after the needling sensation is obtained), whereupon 2 manipulations will be applied at 10-minute intervals before needle removal. During needle retention, far-infrared heat therapy will be applied at the lateral, medial, and anterior sides of the knee for 10 minutes each for a total of 30 minutes while maintaining a 30-cm safety distance (Figure 4). The treated region will be observed and checked for redness at 10-minute intervals to prevent burn injury. A total of 12 acupuncture sessions will be administered twice a week for 6 weeks in addition to standard care. A minimum of 50% attendance (6 of 12 sessions) is required to qualify as completing the study treatment. There are no make-up sessions should the patient miss the scheduled appointment. Total numbers and dates of attended and missed sessions will be recorded for analysis purposes. The study intervention will be conducted at TTSH, CIMC, or SCHMI. The patients are allowed to indicate their preference for the treatment location at the start of the intervention and must attend at the selected location throughout the 6-week intervention. Each TCM session takes approximately 40 minutes, involving acupuncture and heat therapy. Safety precautions will also be exercised to ensure the safety of the patients. Generally, acupuncture is safe and has a low risk of adverse events [37]. However, since the most common adverse events are subcutaneous hematomas and hemorrhages at the site of needling [37], the TCM practitioner will take extra precaution if patients indicate during informed consent that they are taking antiplatelets or anticoagulants. All adverse events that occur during the treatment will be documented.

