#### Standard Care

Standard care generally constitutes simple lifestyle advice, analgesia, and a referral to the outpatient physiotherapist. The physiotherapist conducts an assessment and recommends a variety of lifestyle modifications and exercise therapy. Any other treatment or the involvement of allied health professionals, such as dieticians, will take place at the discretion of the managing physician. The patients in the standard care group will be discouraged from seeking acupuncture treatment for 6 to 8 weeks after randomization. However, if they do so, it will be noted and accounted for in the analysis.

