### Strengths and Limitations

One of the major strengths of our HARMOKnee study is that it follows the gold standard for research design: an RCT. The RCT design guarantees that the research uses a rigorous methodology and controls for potential confounding variables. The likelihood of bias can be reduced through allowing more precise assessment of the intervention’s efficacy. This study also adheres to the STRICTA guidelines, which provide a standardized framework for reporting acupuncture trials. All relevant data will be reported, thereby enhancing the study’s transparency and reproducibility. Moreover, this effectiveness-implementation hybrid study has incorporated an implementation component with the clinical effectiveness assessment. Its benefits include allowing the researchers to maximize the efficiency of their research while collecting data on both effectiveness and implementation, thereby identifying gaps in implementation and increasing the likelihood that the interventions will be effectively implemented and disseminated in real-world settings.

Limitations include the use of a pragmatic study design to mimic real-world conditions as closely as possible. This has an impact in terms of what treatment the control arm receives and how the intervention is delivered. Considerations to ensure intervention delivery fidelity have been incorporated, including standardization and training among acupuncturists. In addition, the treatment that the control arm receives will be meticulously recorded as part of the cost questionnaire and will be included in the analysis. Second, due to logistical and funding limitations, we are only able to include a follow-up period of up to 26 weeks. This will not allow us to establish the long-term effectiveness of this intervention.

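### The supplementary per-protocol analysis counts knee surgery for treatment failure as a protocol violation, so its population is selected on the outcome

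*Protocol article*

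**What the plan says.** Protocol article, Data Analysis Plan: the lead principle is plain, "Results will be analyzed by the intention-to-treat principle". The next sentence adds a second analysis: "However, data will also be analyzed by a per-protocol approach to account for protocol violations". Two examples of such violations follow: "patients who were deemed not compliant to treatment" and "patients who underwent a surgical procedure of the knee due to treatment failure during the study".

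Treatment Regimen gives the only numeric attendance standard: "A minimum of 50% attendance (6 of 12 sessions) is required to qualify as completing the study treatment". Sessions exist only in the intervention arm.

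Two other places bear on treatment received by controls. Standard Care: "The patients in the standard care group will be discouraged from seeking acupuncture treatment for 6 to 8 weeks after randomization", followed by "However, if they do so, it will be noted and accounted for in the analysis". Strengths and Limitations: "the treatment that the control arm receives will be meticulously recorded as part of the cost questionnaire and will be included in the analysis".

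Outcome Measures sets the primary end point as KOOS-12 at week 6. The mixed model in the Data Analysis Plan covers change from baseline to week 26.

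**The concern.** A per-protocol set is meant to remove departures from the protocol. Surgery is not such a departure under this article's own rules: Standard Care leaves other treatment to the managing physician, and Withdrawal Criteria lists opting for knee replacement only as a reason the study intervention may stop. What identifies these patients is that treatment failed. Removing them takes poor results out of both arms, and more of them out of the arm that does worse.

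The attendance rule adds a different selection. If it defines compliance, intervention patients who attend would be compared with nearly all controls, and randomization no longer protects that contrast. With a true effect, the two selections can pull in opposite directions. Agreement or disagreement between the per-protocol and intention-to-treat results would then be hard to interpret.

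Finally, the sentences on control-arm treatment do not say which analysis they concern. If treatment received after randomization became a covariate in the intention-to-treat model, that model would condition on something patients choose partly because of their pain.

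**Working it through.** **Scale, from Sample Size Calculation.** Inputs: difference 10, SD 14, two-sided 5%, power 90%. n per arm = 2 × (1.960 + 1.282)² × 14² / 10² = 41.2, rounded up to 42. The stated 42 reproduces as a per-arm figure. With 50 per arm, the standard error of a difference in means is 14 × √(2/50) = 2.8 points.

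The article gives no surgery rate, no attendance rate and no correlation of either with outcome. All of these below are assumptions.

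**Exclusion of surgery for failure.** Let surgery occur when a standard normal score, correlated r with the outcome, falls below the cut-off z that gives a control rate p. Removing those patients raises the mean of the remaining controls by 14 × r × φ(z)/(1 − p). In the treated arm with a true effect of 10, the cut-off moves to z − r × 10/14. The per-protocol bias is the treated shift minus the control shift.

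Example, r = 0.7 and p = 5%:
- Controls: z = −1.645, φ = 0.1031; shift = 14 × 0.7 × 0.1031/0.95 = 1.06.
- Treated: cut-off −2.145, rate 1.6%, φ = 0.0400; shift = 14 × 0.7 × 0.0400/0.984 = 0.40.
- Bias = 0.40 − 1.06 = −0.67. Simulation gives −0.68.

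| r | control rate | treated rate | bias, true effect 10 |
|---|---|---|---|
| 0.7 | 2% | 0.5% | −0.3 |
| 0.7 | 5% | 1.6% | −0.7 |
| 0.7 | 10% | 3.7% | −1.1 |
| 0.89 | 5% | 1.1% | −1.0 |
| 0.89 | 9% | 2.4% | −1.5 |
| 0.45 | 5% | 2.5% | −0.3 |
| 0.45 | 9% | 4.8% | −0.5 |

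Crossing the extremes widens this only slightly: −0.2 at r = 0.45 and 2%, −1.6 at r = 0.89 and 10%. With no true effect the two shifts are equal and the bias is 0. In a control arm of 50, rates of 2% to 10% mean 1 to 5 patients.

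**One-arm attendance exclusion.** The same shift formula, applied to the treated arm only:
- 10% excluded, φ = 0.1755: 14 × 0.3 × 0.1755/0.9 = +0.8 at correlation 0.3; +1.4 at 0.5.
- 20% excluded, φ = 0.2800: 14 × 0.3 × 0.2800/0.8 = +1.5 at correlation 0.3; +2.4 at 0.5 (2.45 unrounded).
- Correlation 0: no bias at either rate.

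This bias does not depend on the true effect. With no true effect and 42 per arm, the simulated two-sided error rate was 5.8% (10% excluded, correlation 0.3), 7.3% (20%, 0.3) and 11.6% (20%, 0.5).

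**Both exclusions** (5% control surgery at r = 0.7, attendance correlation 0.3, 10% to 20% non-attenders), by simulation: +0.1 to +0.7 points with a true 10-point effect, +0.7 to +1.3 with none.

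**Control-arm acupuncture, only if it were adjusted for or used to exclude.** If 10% to 20% of controls seek acupuncture because they are doing worse (correlation 0.3 to 0.5) and it has no effect on them, removing their contribution raises the control mean by the same 0.8 to 2.5 points and lowers the treatment contrast by that amount.

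**The case against.** The strongest reply is that little depends on this. Intention-to-treat leads and per-protocol is additional. The article does not spell out that patients with surgery are dropped, its examples are introduced as examples, and the full definition may stand in the full protocol (Multimedia Appendix 1) or an analysis plan, neither of which is shown. The primary end point is week 6, when surgery for failure is probably rare. The sizes above come from chosen inputs; they use the raw outcome, whereas the plan analyzes change from baseline, which could absorb part of a prognostic gap. Scores after surgery may reflect the operation rather than the failure, so the direction at later visits is less certain than the calculation suggests.

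All of this limits the size of the point. It does not remove it: the article names failure surgery as a violation, exclusion is the ordinary meaning of per-protocol, and a fuller plan that follows this text would carry the rule forward.

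Four stronger readings are tempting and are not supported:

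- *The main comparison is compromised.* The sentences in Standard Care and in Strengths and Limitations do not say that control-arm treatment enters the intention-to-treat model. They could equally mean description, a sensitivity analysis or, since the second mentions the cost questionnaire, the economic evaluation.
- *The per-protocol result is certainly biased.* It is open to bias. The attendance part is zero if attendance is unrelated to prognosis, and the surgery part is zero without a true effect. The article also does not tie the 6-of-12 rule explicitly to per-protocol compliance, and controls who seek acupuncture might be counted as violators too.
- *Control treatment before week 6 cannot be separated out, because the cost questionnaire is given at baseline, 12 and 26 weeks.* Trial Procedure and Recruitment provides for regular follow-up and recording of medications, Standard Care says acupuncture will be noted, and Outcome Measures adds administrative data on health care use.
- *Per-protocol must give way to a complier-average causal effect.* That is a trade-off: there is no sham control, patients attending 1 to 5 sessions are partly treated, and the interval would be wider in a trial of 100.

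**Conclusion.** The point holds for the supplementary analysis. Classing surgery for treatment failure as a protocol violation makes the per-protocol set depend on the outcome. If the treatment works and more controls than treated patients have surgery, the per-protocol effect tends to be understated by about 0.3 to 1.5 points of 10, at most roughly half a standard error (1.5/2.8 = 0.54). This rests on assumed control surgery rates of 2% to 10%, assumed links between surgery and outcome, and scores that reflect the failure rather than the operation.

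The one-arm attendance rule adds possible selection in the other direction, from 0 to about 2.5 points under the assumptions tried. The net sign is therefore unknown. The intention-to-treat result is not shown to be affected; what is needed there is a clear statement of what the two sentences on control-arm treatment mean.

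**What to change.** 1. Remove knee surgery for treatment failure from the examples of per-protocol violations. Report it by arm as an outcome, and state how KOOS-12 scores collected after surgery are handled, as an intercurrent event.
2. Label the per-protocol analysis as supportive only.
3. State that the intention-to-treat model is not adjusted for any treatment received after randomization. Describe control-arm acupuncture by count and timing, or examine it in a prespecified sensitivity analysis.
4. Optional: a complier-average analysis that uses the recorded session counts, with its assumptions stated.

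The cost is a few sentences of analysis text and slightly more reporting. Items 1 to 3 need no change to sample size, visits or data collection.

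### The primary end point is KOOS-12 at week 6, but the stated analysis of the primary outcome is change to the 26-week follow-up, and no week-6 test is named

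*Protocol article*

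**What the plan says.** The protocol article fixes the time of the primary end point twice. The abstract (Methods) states: "The primary outcome measure is the Knee Osteoarthritis Outcome Score at 6 weeks". Outcome Measures states: "The primary end point in this study is the Knee Osteoarthritis Outcome Score (KOOS-12) at week 6". Under Treatment Regimen the acupuncture course lasts 6 weeks, so week 6 is the end of treatment. Outcomes are collected at baseline and at weeks 6, 12 and 26.

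The Data Analysis Plan then describes the test: "Between-group comparisons of change from baseline to the 26-week follow-up in the primary and secondary continuous outcomes will be analyzed". The method is a generalized linear mixed model, with significance at a two-sided P below .05. The sentence covers the primary outcome by name, and no section names a week-6 comparison.

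The Sample Size Calculation refers to the primary outcome without a week: "The sample size needed to find a 10-point difference for KOOS-12 (the primary outcome) between the intervention and control arms".

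**The concern.** The end point and its test carry different times. Week 6 asks whether the treatment works by the time it stops. Week 26 asks whether a difference is still present about 20 weeks later. Conditions in the control arm also differ between the two. Standard Care says: "The patients in the standard care group will be discouraged from seeking acupuncture treatment for 6 to 8 weeks after randomization". After that window controls are under no such request, and any acupuncture they receive could narrow the difference. The article says such use will be noted and accounted for in the analysis, but does not say how.

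If the analysis sentence is followed as written, a real end-of-treatment benefit that fades could be reported as a negative primary result. Conversely, a result at week 26 or across visits could be reported as if it answered the week-6 question.

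**Working it through.** **1. The sections side by side**

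| Section | Quantity | Time |
|---|---|---|
| Abstract, Methods | Primary outcome, KOOS | Week 6 |
| Outcome Measures | Primary end point, KOOS-12 | Week 6 |
| Sample Size Calculation | KOOS-12, called the primary outcome | None given |
| Data Analysis Plan | Change in primary and secondary continuous outcomes | Baseline to week 26 |

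Treatment ends at week 6, so the last visit is 26 − 6 = 20 weeks after it.

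**2. The plan's own sample size**

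Inputs (Sample Size Calculation): difference 10, SD 14, two-sided alpha 0.05, power 90%. Allocation is 1:1 (Randomization and Concealment of Allocation).

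n per arm = 2 × SD² × (z₀.₉₇₅ + z₀.₉₀)² / difference² = 2 × 196 × (1.960 + 1.282)² / 100 = 41.2, rounded up to 42.

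The t-test version gives 42.2. The stated n=42 is therefore reproduced as a per-arm figure. The arithmetic is not in question here. Because the section calls KOOS-12 the primary outcome, and that is set at week 6 elsewhere, the sizing is taken to be for week 6.

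**3. Power at week 6**

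Evaluable patients: 100 × (1 − 0.20) = 80, or 40 per arm.

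Standard error of the difference = 14 × √(2/40) = 3.13. Then 10 / 3.13 = 3.19, and power by normal approximation is Φ(3.19 − 1.96) = 0.89. The two-sample t-test gives 0.884, about 88%.

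**4. Power if the test is at week 26**

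The documents give no week-26 effect, so the differences below are assumptions. SD 14 and 40 per arm are kept.

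| Assumed week-26 difference | Power, t-test | Power, normal approximation |
|---|---|---|
| 10 (effect fully persists) | 88% | 89% |
| 8 | 71% | 72% |
| 7 | 60% | 61% |
| 5 | 35% | 36% |

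These figures are for a simple two-group comparison at one visit with a constant SD. They do not represent the full mixed model or an effect averaged over visits.

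**The case against.** The strongest reply is that the analysis sentence gives the span of data in the model, not a single week-26 change score. Three things support this. A mixed model is the usual tool for repeated visits and would hardly be needed for one change score. The same sentence covers the secondary continuous outcomes, and the abstract sets these at several visits: "Secondary outcome measures include psychological, physical, quality of life, satisfaction, and global outcome measures at 6, 12, and 26 weeks". On the literal reading, their week-6 and week-12 data would have no between-group analysis. The stated aim also covers both short- and medium-term effectiveness.

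This reading is plausible, and a reader should not infer that a week-26 change score is the only possible meaning. It does not remove the point. A model over weeks 6, 12 and 26 can supply a week-6 contrast, but the sentence does not ask for one. What it describes on this reading is a group effect across visits. Both readings need the same correction.

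A second reply is that details of contrasts belong in the full protocol or the SAP. That holds for an omitted detail. Here the article does state a time for the primary comparison, and it conflicts with the declared end point.

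A reader might also infer that the choice of primary time point is open. The documents do not support that: week 6 is fixed twice, and a later claim that week 26 was primary would visibly contradict both statements.

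**Conclusion.** The point holds: the article declares a week-6 primary end point and describes a test of the primary outcome that is not at week 6. This follows from the text alone and needs no assumption about effects.

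The size of the consequence does rest on assumptions. If the test is at week 26 and the difference has faded to 8, 7 or 5 points, power falls from about 88% to about 71%, 60% or 35%. If 10 points persist, no power is lost, but the test is still not of the declared end point. It would go too far to say that the trial is underpowered or that a fade is expected, since the documents give no week-26 effect. That the trial was sized for week 6 is also an inference, though a short one, from the label used in the Sample Size Calculation.

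**What to change.** In the Data Analysis Plan, state that the primary analysis is the between-group difference in KOOS-12 at week 6, with 95% confidence interval and tested at two-sided 0.05. It is taken as the week-6 contrast from the mixed model fitted to weeks 6, 12 and 26, with baseline accounted for. State that the week-12 and week-26 contrasts are secondary. Adding the week to the Sample Size Calculation would complete the match.

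The cost is wording only. The data, visits, model and 42 per arm are unchanged. The change should be made and dated before the outcome data are analysed.
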